## Abstract

**Background:**

Pancreatic cancer is the third leading cause of cancer-related death in Australia, with a persistently poor 5-year survival rate of around 13%. Symptoms arising from the disease and chemotherapy such as epigastric pain, anorexia, bloating and fat-malabsorptive diarrhoea cause poor oral intake and weight loss, and reduce an individual’s quality of life and ability to tolerate anti-cancer treatment. The primary aim of this study is to determine if an early, intensive telehealth nutrition intervention can improve quality of life compared to usual care for people undergoing treatment for pancreatic cancer.

**Methods:**

This multicentre randomised controlled trial will recruit adults newly diagnosed with borderline resectable, locally advanced or metastatic pancreatic cancer from multiple health services across Victoria (metropolitan and regional). The control group will receive usual nutrition care, which is site-dependent. The intervention group will receive weekly telehealth dietetic consultations for six months, targeting nutritional adequacy through dietary education and counselling, oral nutrition supplement drinks and dietetics-led symptom management advocacy, including appropriate dosing of pancreatic enzymes. Escalation to supplemental jejunal tube feeding may occur if clinically required in the intervention arm. The primary outcome is quality of life (EORTC-QLQ C30 summary score); secondary outcomes include survival, chemotherapy dosing changes, and nutrition status markers including body composition. Outcomes will be measured at baseline, and three- and six-months.

**Discussion:**

The findings of this study will provide evidence of the impact that intensive nutrition therapy, including counselling, provision of oral nutrition supplement drinks and the option for jejunal feeding, has on quality of life and health outcomes in pancreatic cancer. The consistent dietetic approach with the use of telehealth consultations to reduce malnutrition and aid symptom management challenges the current model of care.

**Trial registration:**

31st January 2024, Australian and New Zealand Clinical Trial Registry (Trial ID/No. ACTRN12624000084583).

## Background

Pancreatic cancer is the third leading cause of cancer-related death in Australia, and predicted to be the second leading by 2030, with a persistently poor 5-year survival rate of around 13% [1]. The presence of debilitating symptoms related to pancreatic cancer such as epigastric pain, bloating, loss of appetite, and fat-malabsorptive diarrhoea causes poor oral intake and weight loss, with 80% of patients reporting weight loss prior to diagnosis [2, 3]. These ‘nutrition impact’ symptoms, and the resulting malnutrition, reduce patients’ quality of life (QoL) and length of survival, for example through chemotherapy dose reductions as a result of intolerable chemotherapy side effects [4–6]. Treatment of symptoms contributing to malnutrition in pancreatic cancer is therefore key to improvement in QoL and survival. Our team have previously conducted a two-arm randomised controlled trial investigating the impact of intensive dietary counselling on QoL in upper gastrointestinal (UGI) cancers [7]. In this study, all participants with pancreatic cancer (*n* = 44) experienced at least one nutrition impact symptom prior to commencement of treatment; three-quarters (*n* = 33) of participants experienced more than five symptoms, around half (*n* = 23) experienced more than ten, and one participant experienced 20 different nutrition impact symptoms prior to treatment [8]. Many tumour- and treatment-associated nutrition impact symptoms are not sufficiently controlled with appropriate prescription of medication with chemotherapy-induced nausea and vomiting underestimated (and therefore undertreated) by clinicians [9, 10]. Patients with pancreatic cancer also often experience digestive symptoms associated with pancreatic exocrine insufficiency (PEI) [2]. PEI severity is an independent prognostic determinant, and adequate treatment using pancreatic enzyme replacement therapy (PERT) has been shown to improve survival rates and QoL through alleviation of gastrointestinal symptoms [11, 12]. However, in Australia, PERT is poorly prescribed for patients with pancreatic cancer, with reports of only 21 to 52% of patients with pancreatic cancer receiving it, in part due to a lack of standardised optimal screening pathway to identify PEI [7, 13, 14].

Dietitians are experts in clinical nutrition and are trained to provide nutrition support, advocate and strategise for effective control of symptoms that arise from chemotherapy and PEI [15]. Strategies such as dietary education, counselling and the provision of nutrition support either via the oral route, including the use of oral nutrition supplement drinks or via the enteral route using a feeding tube, are used by dietitians to optimise nutritional intake of patients. Dietitians are important members of the cancer multidisciplinary team; however, evidence suggests that only up to half of patients with pancreatic cancer are consulting with dietitians [16, 17]. Our previous study demonstrated that control group participants with pancreatic cancer who received ‘usual nutrition care’ waited an average of 82 days before first contact with a dietitian, with some never seeing a dietitian [7]. Routine malnutrition screening does occur in most health services across Australia, but barriers to intervention include screening not occurring early enough in a patient’s cancer journey, or the out-of-pocket costs associated with some dietitian services, or the specialist expertise of the dietitian [18–20] An additional barrier to early nutrition intervention is the ability of patients to physically access dietetic services face-to-face [21, 22]. Patient perspectives on early telehealth-based interventions to overcome this barrier were investigated in a qualitative study exploring acceptability of different models of nutrition care delivery to patients undergoing treatment for UGI cancers [21]; given the significant physical and emotional burden that cancer diagnosis and treatment places on patients, the convenience and flexibility of telehealth intervention at home was widely preferred [21, 23].

The aim of this study is to determine if early, intensive nutrition intervention comprising dietary education and counselling, provision of oral nutrition supplement drinks, proactive symptom control and the use of jejunal enteral feeding as needed, can improve health-related quality of life in people with newly diagnosed pancreatic cancer. In addition, compared to usual care, the intervention may improve survival length, chemotherapy dosing, nutrition status, symptom burden and economic measures (Fig. 1).

**Fig. 1 Fig1:**
[figure not shown]
Precipitants and consequences of malnutrition

The proposed intervention involves dietary education and counselling commencing earlier and occurring more frequently than usual care, as well as provision of oral nutrition supplement drinks, effective symptom management and escalation to enteral feeding as needed. It is hypothesised that the intervention will address the many precipitants of cancer-associated malnutrition (denoted in bold text on the left of the circle) and reduce the subsequent risk of poor outcomes associated with malnutrition (denoted in bold on the right of the circle). Outcomes denoted with an asterisk will be measured in this study.

## Methods

### Study design

This study is a two-arm, multicentred, randomised controlled trial. Outcomes will be measured at baseline, three, and six-month follow-up time points. Figure 2 represents the study design and participant flow.

**Fig. 2 Fig2:**
[figure not shown]
Study flow chart

The study flow chart depicts the two pathways; the intervention and usual care group. The usual care group will be screened for malnutrition at their healthcare services and will be referred to a dietitian when clinically indicated. Those in the intervention group will receive weekly telehealth dietitian interventions.

### Participants and setting

This study will recruit patients with newly diagnosed borderline resectable, locally advanced or metastatic pancreatic cancer who will be receiving or have already received one cycle of chemotherapy treatment across Victorian health care services. Regional and rural health care services are included in participating sites to help reduce inequities across cancer care as demonstrated in the Australian Cancer Plan [24].

### Eligibility

Individuals aged > 18 years with a diagnosis of pancreatic cancer by radiological imaging, and/or biopsy and/or multidisciplinary agreement, that are expected to survive at least six months from diagnosis will be screened for eligibility to participate. Patients will also require an Eastern Cooperative Oncology Group (ECOG) Performance Status Scale is two or less to be eligible [25]. Those with neuroendocrine pancreatic cancers or who have previously undergone pancreatic cancer surgical resection will be ineligible. Those who decline or who are unsuitable for systemic chemotherapy, will also be ineligible. Patients will not be eligible to participate if they have serious medical or psychiatric conditions that might compromise protocol-based management as judged by the patient’s treating healthcare team. Individuals with insufficient cognition or knowledge of the English language as determined by the treating healthcare team, who do not have a family member who can assist with English translation to facilitate the completion of outcome data collection or interviews with the study dietitian will also be ineligible to participate.

### Recruitment

Potential eligible individuals will be identified by site study representatives at each health service through their multidisciplinary meetings and oncology or endoscopy clinic lists. Once identified, site study representatives will screen the patient based on the inclusion criteria, and if eligible will contact the patient via phone or in person to invite them to participate. The details of the study will be provided to patients through the Participant Information and Consent Form (PICF). Patients will be invited to discuss their participation in the study with a support person who can assist in the decision-making, such as a family member, friend, or their oncologist or general practitioner. Patients will have the opportunity to ask the investigators further questions about the study as required. To enrol in the study, patients will sign an e-consent form via REDCap or a paper copy of the consent form, which will be documented according to Good Clinical Practice Guidelines [26, 27]. Once enrolment is confirmed, participants will be sent a link to a baseline questionnaire on REDCap or via email with a document attached, with the additional option of completing this over the phone or in person with a research assistant if preferred.

### Randomisation and blinding

The random allocation sequence will be developed by a statistician who has no role in the recruitment of participants or data collection. Dynamic randomisation methods will be employed using STATA 18, based upon dichotomisation of malnutrition risk score at baseline assessment (Patient Generated Subjective Global Assessment Short Form (PG-SGA_SF_) score of < 12 vs. ≥ 12 based on distribution of baseline scores from our previous research) cancer stage (borderline resectable or locally advanced vs. metastatic), and commencement of chemotherapy (yes vs. no) [7, 28, 29]. The randomisation sequence will be generated by the study project managers and kept in a password-encrypted file. The project managers will contact the intervention dietitian and provide the sequential participant registration number. Participants will be informed of their group allocation via phone by the intervention dietitian.

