### ‘Usual care’ control group

Routine dietetic care will be received by those participants randomised to the control group, also known as usual nutrition care. Usual care most commonly involves nurse-led malnutrition screening at each chemotherapy visit or acute inpatient admission, with patients at risk of malnutrition referred to a dietitian for nutrition assessment and intervention to optimise nutrition status. The timing and delivery of usual care will differ between health services.

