### Intervention group

The intervention will be provided in addition to usual care for a duration of six months. The intervention differs to usual care in terms of the mode, frequency and intensity of dietetic involvement. Dietitians will complete training in Behaviour Change Technique Taxonomy v1 (BCTT – V1) and all aspects of the intervention including symptom management, nutrition counselling, provision of oral nutrition supplement drinks, enteral nutrition regimen development and feeding tube management [30]. To reduce barriers to nutrition care, the nutrition intervention will be delivered via telehealth making it more widely accessible for a larger population, with the mode (telephone or videolink) determined by participant preference [21, 22]. Dietetic consultations will occur weekly at a minimum, as previous studies have displayed that consistent dietetic interactions can create a sense of support and rapport leading to greater engagement and disclosure of symptoms [21]. The intervention dietitian will contact participants as soon as practicable after randomisation to complete the initial nutrition assessment, and to arrange postage of a resource pack to participants. The pack contains an information booklet outlining key contacts, weight record templates, common side effects of treatment and how to manage them, and nutrition intervention strategies and education. The intervention dietitian will refer to the participant booklet during consultations, as a guide for dietary education and counselling. The booklet al.so outlines enteral feeding information including daily care of feeding tubes and a section to document individualised regimens for those that receive a tube. The participant can choose to record information in the booklet, such as medication changes or timing of symptoms, to report back to the intervention dietitian during weekly consults. Participants will also receive a diary to record PERT dosages, a PERT education booklet, and a pill box to store PERT capsules, as well as samples of oral nutrition supplement drinks to trial. Provision of trial supplement drinks will be tailored as required, depending on participants’ medical history e.g. participants with poorly controlled diabetes mellitus.

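### The intervention dietitian phones controls with their allocation: one avoidable contact between the control arm and the person delivering the tested intervention

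*Protocol article*

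**What the plan says.** Under *Randomisation and blinding*, the protocol article has the project managers generate the allocation sequence, and then: "The project managers will contact the intervention dietitian and provide the sequential participant registration number". The next sentence is: "Participants will be informed of their group allocation via phone by the intervention dietitian".

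The control condition is set out separately. The section *'Usual care' control group* says: "Routine dietetic care will be received by those participants randomised to the control group, also known as usual nutrition care". It describes nurse-led malnutrition screening, with at-risk patients sent on to a dietitian, and says that timing and delivery vary by site. The caption to Fig. 2 says the usual care group "will be referred to a dietitian when clinically indicated".

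For the active arm, the *Intervention group* section provides its own first contact: "The intervention dietitian will contact participants as soon as practicable after randomisation to complete the initial nutrition assessment". It also says that consultations take place by telephone or video link, as the participant prefers.

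**The concern.** The trial tests early and intensive dietetic involvement delivered remotely. The comparison is cleanest if controls meet only what their own health service would give them. A call from the intervention dietitian gives each control an exchange with the person who delivers the tested treatment, by telephone and just after randomisation.

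That dietitian is trained in symptom management, nutrition counselling and behaviour change techniques. The *Background* reports that every participant with pancreatic cancer in the group's previous trial had at least one nutrition-related symptom before treatment. A control with symptoms, on the phone with a dietitian and hearing that the programme will not be offered, could well ask a question. If advice or a suggestion to seek referral followed, a little of the intervention would have reached the control arm. Nothing in the design needs this contact to exist.

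**Working it through.** The point contains no figure, so the check is a reading of the relevant sections against each other.

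1. **Does the sentence cover controls?** It stands in the trial-wide section on randomisation, not under *Intervention group*. It speaks of participants and of the group each was allocated to, which makes most sense if both groups are meant. No other way of telling controls appears in the article. One limit: the *Intervention group* section uses the bare word *participants* for that arm alone, so the word does not settle the matter by itself. The both-arms reading is the natural one, but it is an inference.

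2. **Would usual care provide this contact?** No. *'Usual care' control group* and the Fig. 2 caption give one route to a dietitian, which is screening followed by referral, and that dietitian belongs to the health service. A call from the study's intervention dietitian is outside that route.

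3. **Does the contact resemble the intervention?** It does in three respects: the provider is the same, telephone is one of the two stated delivery modes, and the timing is immediately after randomisation. It does not in content, because the stated purpose is only to give the allocation.

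4. **When does it fall relative to measurement?** *Blinded outcomes* places the baseline quality-of-life survey before allocation. The call therefore comes after baseline and before the three-month assessment. Any effect it had would fall within follow-up and would not be removed by adjusting for baseline.

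5. **Is the dietitian needed for the call?** No. The project managers generate the sequence and tell the dietitian, so they already hold what has to be passed on. Intervention participants lose nothing, because the dietitian's initial assessment contact is a separate step.

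6. **How large is the exposure?** It is one call per control, with a planned 41 controls (*Power calculation*). The intervention arm has consultations at least weekly for six months, about 52 / 2 = 26, together with supplement drinks, enzyme guidance and the option of tube feeding. One call with an administrative purpose is small beside that. The article gives no figure from which an effect on the primary outcome could be derived.

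**The case against.** The strongest reply is that the article describes a notification and nothing more. No sentence says that symptoms are discussed or advice given. Whether the call is scripted is the kind of operational detail that an article leaves to the full protocol. Controls also have other prompts: they complete quality-of-life and malnutrition questionnaires, undergo physical assessments, and are screened at chemotherapy visits. One call adds little to these.

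Most of this stands. The silence on content is not itself a fault, and it means that dietetic treatment of controls is not shown. What remains is the choice of caller, which the article does state and which could be made differently at almost no cost.

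Three stronger readings are tempting and are not supported:

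- *That controls' first dietitian contact moves from 82 days to day 0.* The *Background* says that controls with pancreatic cancer in the previous trial "waited an average of 82 days before first contact with a dietitian, with some never seeing a dietitian". That figure describes access to dietetic care under usual care. Being told an allocation is not dietetic care, so the call does not move it.
- *That any effect can only shrink the difference.* Advice or referral would tend to do so. But the primary outcome is self-reported by participants who know their arm, and a control disappointed by the news could report worse quality of life, which would widen the difference. The direction is not fixed.
- *That the call compromises data extraction.* *Database extraction* gives intervention dietitians access to the hospitals' medical records whoever makes the call, so moving the call changes nothing there.

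**Conclusion.** The point holds as a minor, avoidable design weakness. As written, the plan has the intervention provider phone controls, a contact that usual care would not include. This is an opportunity for contamination and not demonstrated contamination. It rests on one assumption, that the unrestricted sentence covers both arms. If controls are in fact told another way, the sentence is inaccurate and needs correcting for that reason.

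The effect on the result is probably small and cannot be quantified from the document. A reader might try to express it as lost power. The plan's own sample size does reproduce: with a correlation of 0.41, one baseline and two follow-ups, the variance factor is (1 + 0.41)/2 − 0.41² = 0.5369, and 2 × ((1.960 + 0.842)/0.50)² × 0.5369 = 33.7, so 34 per group with 80.3% power. Shrinking the effect by 10% to 0.45 would give 71.6%. That arithmetic is correct, but nothing in the article supports 10%, or any other non-zero dilution, for a single notification call. It should not be cited as the size of this problem.

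**What to change.** Reword the sentence under *Randomisation and blinding* so that a project manager, or another unblinded staff member with no dietetic role, tells participants their allocation by phone from a short fixed script. At the least this should apply to controls. State that the intervention dietitian contacts intervention participants only, through the initial assessment contact already described under *Intervention group*. If controls are already told by someone else, say so.

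The cost is one short call per participant by staff who already hold the allocation. The sample size, the outcomes, the analysis and the intervention itself are unchanged.

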### ‘Usual care’ control group

Routine dietetic care will be received by those participants randomised to the control group, also known as usual nutrition care. Usual care most commonly involves nurse-led malnutrition screening at each chemotherapy visit or acute inpatient admission, with patients at risk of malnutrition referred to a dietitian for nutrition assessment and intervention to optimise nutrition status. The timing and delivery of usual care will differ between health services.

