### Intervention fidelity and safety secondary outcomes

Intervention fidelity measures will be undertaken to understand the degree to which the intervention was able to be delivered as planned. These include: provision of oral nutrition supplements and consumption, PERT recommendations, medication recommendations, referrals to support services, feeding tube insertions, and feeding tube complications.

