### Power calculation

A two-group comparison power analysis using the primary outcome, a power of 80%, and two-tailed alpha of 0.05 was undertaken. We considered that the minimum standardised effect that would be needed to justify the cost of the intervention would be a delta of 0.50 (large effect). In absolute terms, this is a change of 0.15 in health utility (scale value of 1 = perfect health, value of zero = death) given a standard deviation in our TEND study data of 0.29 for health utility at baseline [7]. With these inputs and considering inclusion of a baseline measurement and two follow-up measurements (3 months and 6 months) with correlation between them of 0.41 (based on data from our previous randomised controlled trial) in the model, we calculated that we would need *n* = 34 participants per group. We increased this requirement by 20% to *n* = 41 per group to account for potential loss to follow-up or missing data.

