### Data analysis

#### Primary and secondary trial outcomes

Analyses will be undertaken on an intention-to-treat basis. The primary outcome (EORTC QLQ-C30 summary score) will be compared between groups using a linear mixed model analysis approach, using values collected at three and six months, and adjusting for baseline values of this variable as well as age, sex, cancer stage, and malnutrition risk score (PG-SGA_SF_ score) [29, 43]. Group allocation will be treated as a fixed effect, while individual participants and assessment time points will be treated as random effects. We will conduct relevant checks of distributional assumptions and model fit. Twelve-month mortality will be compared between groups using Cox proportional hazards regression analysis, adjusting for baseline values of health-related quality of life (EORTC QLQ-C30 summary score), as well as age, sex, cancer stage, and malnutrition risk score (PG-SGA_SF_ score) [29, 43]. Multiple imputation will be used in the event of missing data with checking or relevant assumptions for missing-ness to inform the final imputation approach [55].

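### Usual care differs by site on the protocol's own account, yet site is neither balanced in allocation nor a term in the models, so a chance site imbalance would go into the estimate uncorrected

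*Protocol article*

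**What the plan says.** The article states twice that the comparator depends on the site. The Methods part of the abstract says "The control group will receive usual nutrition care, which is site-dependent", and the section on the usual care control group says "The timing and delivery of usual care will differ between health services". Sites are drawn from several metropolitan and regional services in Victoria. Their number is not given.

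Under Randomisation and blinding, "Dynamic randomisation methods will be employed using STATA 18, based upon dichotomisation of malnutrition risk score at baseline assessment"; the other two factors are cancer stage and whether chemotherapy has begun. Under Primary and secondary trial outcomes, the mixed model compares groups "adjusting for baseline values of this variable as well as age, sex, cancer stage, and malnutrition risk score", with participant and time point as random effects. The Cox model for 12-month mortality has the matching covariates. Neither site nor region appears in any of these lists.

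Under Intervention group, the intervention is described as an addition to usual care, so a site's usual care reaches both arms.

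**The concern.** When a protocol names a source of variation in its own comparator, one expects that source to be balanced at allocation, adjusted for in the model, or both. Here it is neither. With 41 per arm spread over several services, arms can differ by chance in where their participants are treated. If outcomes differ between services, through usual care or case mix, that difference becomes part of this trial's estimated effect and the stated model leaves it there. Whatever precision site could have supplied is also given up.

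**Working it through.** **1. The plan's own figure.** Inputs from Power calculation: standardised effect 0.50, two-sided alpha 0.05, power 80%, one baseline and two follow-ups, correlation 0.41.

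- Without repeated measures: 2(1.960 + 0.842)² / 0.50² = 62.79 per group.
- Variance factor for the baseline-adjusted mean of two follow-ups: f = (1 + 0.41)/2 − 0.41² = 0.5369.
- 62.79 × 0.5369 = 33.71, so 34 per group. Then 34 × 1.2 = 40.8, so 41.

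The stated size reproduces and is not in dispute. It makes no allowance for site. With 34 evaluable per arm, the standard error of the contrast is √(2 × 0.5369/34) = 0.178 SD.

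**2. How large can a chance shift be?** Assumptions, since the article gives no figures: 4 or 8 sites with sizes proportional to 1, 1/2, 1/3 and so on; site variance v of 1%, 5% or 10% of the unadjusted outcome variance; 68 evaluable participants; 1:1 individual allocation that ignores site. If site k holds share wₖ, the between-arm difference in that share has variance about 4wₖ(1 − wₖ)/68, so

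SD of shift = √[v × 4(1 − Σwₖ²)/68].

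For 4 sites Σwₖ² = 0.328, and for 8 sites 0.207. Example: 4 sites, v = 0.05 gives √(0.05 × 4 × 0.672/68) = 0.044 SD. The 95th percentiles below are simulated (3,000 runs per scenario).

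| Sites | v | SD of shift | 95th percentile of absolute shift |
|---|---|---|---|
| 4 | 1% | 0.020 | 0.04 |
| 4 | 5% | 0.044 | 0.09 |
| 4 | 10% | 0.063 | 0.13–0.14 |
| 8 | 1% | 0.022 | 0.04 |
| 8 | 5% | 0.048 | 0.10 |
| 8 | 10% | 0.068 | 0.13–0.14 |

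The shift averages zero. The largest between-arm difference in any one site's share has a median of 12 percentage points and a 95th percentile of about 24 to 27. The 10% case is generous: after baseline adjustment it is 0.10/0.537 = 19% of the remaining variance.

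**3. A two-group illustration.** Suppose 25 of 82 participants (30%) come from one group of services. Under a hypergeometric split into 41 and 41, the between-arm difference in that share has SD 10 points. It reaches 10 points in 34% of trials and 15 points in 15%. If the share is 20 to 40%, 10 points or more occurs in 16 to 37%. If the grouping explains 5 to 10% of variance, the groups differ by √(0.05/0.21) = 0.49 to √(0.10/0.21) = 0.69 SD, so a 10-point imbalance moves the estimate by 0.05 to 0.07 SD.

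**4. Error rate and power.** Without a site term, the simulated type I error is 4.8 to 5.4%. Power at a true effect of 0.50 SD, first with site fixed effects (3,000 runs) and then, in a separate simulation, with a random site intercept fitted by REML (4,000 runs); Monte Carlo error is about 0.7 points:

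| Sites | v | No site → fixed effects | No site → random intercept |
|---|---|---|---|
| 4 | 1% | 80.2 → 78.1 | 79.0 → 79.3 |
| 4 | 5% | 81.4 → 81.6 | 80.0 → 81.9 |
| 4 | 10% | 81.3 → 84.8 | 82.7 → 86.7 |
| 8 | 1% | 80.0 → 76.3 | 79.4 → 80.0 |
| 8 | 5% | 79.3 → 78.6 | 79.8 → 81.4 |
| 8 | 10% | 80.0 → 81.8 | 80.4 → 84.7 |

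Fixed effects can lose almost 4 points. A random intercept loses none. It gains about 0 to 2 points up to v = 5% (about 9% of the variance left after baseline adjustment) and about 4 only at the generous 10%. Its type I error was 4.8 to 5.7%.

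**The case against.** The strongest reply is that nothing is invalid. Individual randomisation makes site imbalance random error, and that error is already inside the standard error. This stands, and it rules out the stronger reading that site is confounded with treatment, or that a null result could not be told apart from controls happening to sit at well-served sites. The documents do not support that reading for a second reason: because the intervention is added to usual care, good local care is not confined to controls.

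Three further inferences should be resisted.

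- The Background's average 82-day wait for a dietitian comes from controls in an earlier trial and is not attributed to site. There are two statements of site-dependence, not three.
- The article says care differs between health services. It does not say that it differs between metropolitan and regional ones, so that split is only a convenient grouping.
- It is tempting to say that control-arm care goes unmeasured because "Intervention fidelity measures will be undertaken to understand the degree to which the intervention was able to be delivered as planned". That section does not restrict its measures to one arm, and Economic evaluation collects claims data, admissions, procedures and reports of private dietitian use. Detail such as the date of first dietitian contact may sit in the full protocol.

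It is also fair to say that three prognostic balancing factors are defensible in a trial of 82, and that the gain from a fourth is modest.

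One defence does not carry. An unseen SAP might add a model term, but the article sets out the covariates and random effects as its model, and no SAP can add an allocation factor for participants already randomised.

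**Conclusion.** The point holds as one of efficiency and chance imbalance, not of bias. A source of comparator variation that the protocol itself declares is neither balanced nor modelled. The estimate is unbiased in expectation and the test keeps its level. In the single realised trial, an uncorrected shift of up to about 0.04 to 0.14 SD (95th percentile) is possible, which is 8 to 28% of the 0.50 SD target. That range rests on 4 or 8 sites of unequal size and on site explaining 1 to 10% of outcome variance, none of which the documents supply. Neither balancing nor a site main effect deals with a treatment effect that differs between sites because usual care differs. That is a separate question and needs its own summary.

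**What to change.** - **Primary model (Primary and secondary trial outcomes):** add a random intercept for site to the linear mixed model. Do not use fixed effects for many small sites.
- **Cox model:** add a site frailty, or stratify by site group.
- **Allocation (Randomisation and blinding):** for any allocations still to be made, add site as a dynamic-randomisation factor, with small services grouped by a rule fixed in advance.
- **Reporting:** give a descriptive summary of the treatment effect by site group, labelled as descriptive.

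The cost is one extra variance parameter, slightly looser balance on the other three factors and one more input to the allocation program. With few sites the site variance may be estimated as zero. The model then reduces to the one now stated, and the plan should say in advance that this result is accepted. The benefit is small but comes at almost no price.
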